**Methods:**

The current study is a type 1 hybrid effectiveness-implementation trial to evaluate the impact of a proactive, opt-out tobacco treatment intervention on cessation outcomes and advance understanding of key barriers and facilitators of implementation processes. A total of 230 PWH who smoke will be recruited from an infectious diseases clinic at an academic medical center and will be randomized to receive (1) treatment as usual (TAU) or (2) Proactive Outreach with Medication Opt-out for Tobacco Treatment Engagement (PrOMOTE). Primary outcomes include: biochemically verified 7-day point prevalence abstinence (PPA) rates, continuous abstinence (Weeks 9–12), and the number of 24-hour quit attempts at the end of study treatment (Week 12). Secondary outcomes include: participant reach (proportion reached out of contact attempts), implementation fidelity (including number of prescriptions written), participant adherence to prescribed pharmacotherapy, acceptability (participant and provider satisfaction with intervention delivery and content), and perceived barriers.

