Participants will have their study drug covered by their health insurance and mailed to their home (or picked up at a pharmacy). This may include the AIDS Drug Assistance Program (ADAP) if they are uninsured, or 340B funds can be used to cover co-payments if the medication is not fully covered by their health insurance. All participants will be encouraged to start their medication as soon as they receive it and to set a quit date 1 week from medication initiation. The varenicline prescription will follow the standard titration schedule. Participants will remain on varenicline for 12 weeks total. Dose adjustments (e.g., reduction to 0.5 mg twice per day if 1 mg twice per day is not well-tolerated) will be allowed at the discretion of the clinical pharmacist. The dual NRT (or single NRT add-on to other pharmacotherapy such as varenicline or bupropion) prescription will follow standard dosing recommendations. Switching to the other pharmacotherapy (from varenicline to dual NRT or vice versa) will be permitted if the participant reports treatment failure or high frequency of side effects after 1 week of appropriate use, based on the clinical judgement of the pharmacist.

A novel alert system will be built in to the adverse event surveys (see “Assessments”) within the REDCap database such that any severe physical adverse events (e.g., severe nausea, severe sleep disturbances, severe changes in mood) that are endorsed along with self-report of smoking cessation pharmacotherapy use will trigger an alert to the pharmacist. This alert system is intended to improve varenicline (or NRT) medication adherence as the pharmacist can quickly follow-up on any side effects that may be associated with pharmacotherapy use and call the participant with any recommended dose adjustments.

Follow-up: Participants in both study arms will be asked to complete the following surveys: tobacco use calendar, use of pharmacotherapies, quit attempts, adverse events, and psychiatric events (see “Assessments” below) every 2 weeks after randomization. The assessments will be completed via participant interview by research staff over the phone or remotely via REDCap from a smartphone or a computer. Additional assessments will be completed at the Week 12 and Week 24 follow-ups. Participants will also complete a blood draw at Week 12 and 24 to measure CD4/CD8 cell counts and HIV-1 RNA viral load. Participants will be paid $50 for completion of each follow-up interview.

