### Measures

Participants will complete a series of baseline measures at their first meeting by phone or through REDCap’s automated survey feature, including assessments of demographics, smoking behavior (including electronic cigarettes; behavioral risk factors (Behavioral Risk Factor Surveillance System [BRFSS][43]), alcohol (Alcohol Use Disorders Identification Test-C [AUDIT-C][44]) drug use and misuse (including marijuana[43]; Drug Abuse Screening Test-10 [DAST-10][45]), health, and HIV infection history. The Fagerström Test for Nicotine Dependence (FTND) will be completed at baseline to assess the severity of dependence on nicotine.[46–48] Participants will also verify their list of current medications, including ART regimen. Quantity and frequency estimates of tobacco, e-cigarettes, and alcohol use will be assessed using a Timeline Follow-Back Procedure starting 30 days prior to intake (repeated biweekly post-randomization until Week 12 and at the Week 24 follow-up).[49] Number of quit attempts and number of 24-hour quit attempts will be assessed using a similar calendar method biweekly from Weeks 2–12 and at the Week 24 follow-up. The Medication Adherence Questionnaire (MAQ) will be completed at baseline to assess each participant’s history of medication adherence.[50, 51].

 Participants will be assessed regarding their level of knowledge and attitudes toward varenicline and NRT at baseline and at Week 24. Additionally, every 2 weeks they will be asked if they received (PrOMOTE) or received/filled (TAU) their pharmacotherapy prescription (yes/no). The amount and frequency of smoking cessation pharmacotherapy used (per product) will be determined by utilizing the calendar method of data collection described above for tobacco use. Adherence to the smoking cessation pharmacotherapy regimen will also be calculated and will be defined as 80% or more of prescribed doses taken and will be calculated based on the self-report data from this assessment. Motivation and confidence to quit smoking will be assessed using a modification of the Contemplation Ladder[52, 53] which assesses readiness to quit in the next month.

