### Primary outcomes

Primary outcomes of smoking abstinence are defined as biologically-confirmed, end of treatment (EOT) 7-day point prevalence abstinence (Week 12) as well as 4 week continuous abstinence (CA; weeks 9–12).[57] Daily smoking diaries coupled with a breath CO ≤ 5 parts per million (ppm) will be utilized to determine abstinence.[57] To assess number of quit attempts, participants will be asked how many quit attempts and how many 24-hour quit attempts they made concurrent with each tobacco use calendar entry. The number of 24-hour quit attempts during study treatment will be tabulated and assessed at EOT.

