### Planned analyses

Baseline clinical and demographic characteristics will be collected and preliminary analyses will examine significant correlates of study outcomes. Characteristics found to be significantly associated with primary outcome measures will be included as covariates in the initial stages of adjusted model development. Exploratory analysis of the modifying effects of participant sex on study outcomes will be assessed through main effects and the interaction between sex and study treatment assignment. Where significant interactions are found, sex-stratified analyses will be conducted to determine what role sex plays in the effect of varenicline on smoking outcomes in PWH. All statistical analyses will be conducted using the intent-to-treat (ITT) principal and will be completed using SAS v9.4 software.[66].

Clinical efficacy hypothesis: The primary study outcome of interest are the efficacy of PrOMOTE as compared to TAU in achieving biologically confirmed 7-day PPA and 4-week CA from cigarettes at EOT in PWH. To test these hypothesis, logistic regression models utilizing the sandwich variance estimate[67] will be developed. An ITT analysis will be utilized assuming participants that were lost to follow-up and those who withdrew from the study are smoking. Additionally, a completer analysis (participants who complete the Week 12 assessment) will be compared to the ITT results.

Additionally, participants will report all treatment emergent 24-hour quit attempts during study treatment (through Week 12). A Poisson distribution will be assumed with a logarithm link function to assess the effects of PrOMOTE on the number of quit attempts made as compared to TAU. Over-dispersion due to a wider than expected distribution in discrete count models (from heterogeneity) can have a significant impact on parameter inference, thus when detected, a negative binomial (NB) distribution will be specified.

Further, changes in CD4 and CD8 cell counts and the proportion of participants with detectable vs. undetectable HIV-1 RNA viral load will be examined from study baseline to Week 12 and Week 24, and participants who do and do not achieve abstinence will be compared at each timepoint. Generalized linear mixed effects regression models with appropriate distributions will be utilized to make comparisons. Model covariates will include baseline characteristics that were associated with follow-up abstinence.

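### The primary count of 24-hour quit attempts does not rise steadily with benefit, so its arm ratio cannot be read without the abstinence results

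*Protocol article*

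**What the plan says.** The abstract of the protocol article names three primary outcomes: 7-day point prevalence abstinence, continuous abstinence in Weeks 9–12, and the number of 24-hour quit attempts at Week 12. The Primary outcomes section defines the third as a total: "The number of 24-hour quit attempts during study treatment will be tabulated and assessed at EOT". Collection is described under Measures: "Number of quit attempts and number of 24-hour quit attempts will be assessed using a similar calendar method biweekly from Weeks 2–12". Procedures gives both arms the same two-weekly schedule.

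The model is in Planned analyses: "A Poisson distribution will be assumed with a logarithm link function to assess the effects of PrOMOTE on the number of quit attempts made". For over-dispersion the section adds: "thus when detected, a negative binomial (NB) distribution will be specified". It mentions no offset, person-time or time at risk. The only missing-data rule is written for abstinence: "An ITT analysis will be utilized assuming participants that were lost to follow-up and those who withdrew from the study are smoking".

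Planned analyses presents the two abstinence measures as the main outcome and then adds the count. Power and sample size covers the abstinence measures only.

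**The concern.** An outcome used to compare arms should move one way as patients do better. This count does not. Someone who never tries scores 0, someone who quits for good scores 1, and someone who fails three times scores 3. Moving a participant from the first group to the second raises the count; moving one from the third to the second lowers it. Part of PrOMOTE's follow-up counselling is relapse prevention, which, where it works, removes repeat attempts. A better abstinence result could therefore come with a lower count on a primary outcome where more attempts would naturally be taken as better.

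A second, separate issue is that the count accumulates over six two-weekly reports (Weeks 2 to 12). A participant who leaves after Week 4 supplies two of them. Counting a dropout as smoking says nothing about how many attempts fell in the unobserved weeks.

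**Working it through.** **The plan's own figures.** None is given for the count. The abstinence sample sizes do reproduce (two-sided 5%, 80% power, arcsine formula): 94.7, rounded up to 95, for 15% versus 32%; 96.3, rounded up to 97, for 10% versus 25%; and 97/(1 − 0.15) = 114.1, rounded up to 115 per arm. The sample size is not in question.

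**Inputs.** From Power and sample size: abstinence at Week 12 of 32% (PrOMOTE) and 15% (TAU). Assumed, because the article does not give them: the proportion attempting, one attempt per abstainer, and m attempts on average for the others.

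**Version A: 80% of each arm attempts; attempters who do not end abstinent average m.** Mean = p + (0.80 − p) × m.
- m = 2: PrOMOTE 0.32 + 0.48 × 2 = 1.28; TAU 0.15 + 0.65 × 2 = 1.45; ratio 0.88.
- m = 3: 1.76 / 2.10 = 0.84.
- m = 1: 0.80 / 0.80 = 1.00.

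**Version B: all non-abstainers, including those who never try, average m in both arms.** Mean = p + (1 − p) × m.
- m = 0.5: 0.66 / 0.575 = 1.15.
- m = 1: 1.00 / 1.00 = 1.00.
- m = 2: 1.68 / 1.85 = 0.91.
- m = 3: 2.36 / 2.70 = 0.87.

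**Sensitivity to the assumptions.**
- Proportion attempting (version A, m = 2, PrOMOTE at 80%): the ratio is 1 when 0.15 + (a − 0.15) × 2 = 1.28, so a = 71.5% in TAU. At a = 60% the TAU mean is 1.05 and the ratio 1.22 in favour of PrOMOTE. At m = 3, break-even is a = 68.7%.
- Attempts among non-abstainers (version B): PrOMOTE's average must reach 2.25 against 2 in TAU (12.5% more), or 3.5 against 3 (16.7% more), to bring the ratio back to 1.
- Definition of abstainer (version A, m = 2): the planned continuous-abstinence rates of 25% and 10% give 1.35 / 1.50 = 0.90. If abstainers also average 2 attempts, the ratio is 1.00.

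**Would an offset cure this?** Version B was simulated with 115 per arm, 15% dropout among non-quitters in each arm, Poisson regression with robust standard errors and 600 runs per setting. The ratio without an offset was 0.92 at m = 2 and 0.88 at m = 3, significantly favouring TAU in 13% and 27% of runs. With a calendar-time offset the ratios were 0.91 and 0.87. The offset leaves the problem where it was.

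**Unequal follow-up, no true effect.** Ratio = (r₁ + (1 − r₁)f) / (r₂ + (1 − r₂)f), where r is retention and f the share of the 12 weeks observed in dropouts. With an assumed 85% versus 75%:
- f = 1/2: 0.925 / 0.875 = 1.06.
- f = 1/3: 0.900 / 0.833 = 1.08.

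With equal retention the ratio is 1.00 for any f. In simulations with unequal dropout, a calendar-time offset brought the ratio back to about 1.00.

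**The case against.** The strongest reply is that equal attempting in both arms assumes away what PrOMOTE is designed to do. Its counselling works towards commitment to a quit attempt and its participants are encouraged to set a quit date, while TAU is opt-in and the trial enrols people of low motivation too. A modest gap in attempting, 80% against 71.5%, removes the reversal. This stands. It makes the reversal conditional, but it does not make the count monotone: a true gain in attempts can still be offset by fewer repeat attempts and appear as no difference.

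Point prevalence at Week 12 covers only seven days, so those abstainers need not have quit once and for all. That also stands, and it weakens the effect.

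On follow-up, the window is the same 12 weeks for everyone, both arms complete the same surveys, and a single 15% attrition rate is anticipated. An offset is also the kind of detail an article leaves to a fuller document. So its absence is not an error in itself, and nothing in the article predicts unequal retention.

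A reader might infer that the missing exposure term is what penalises early success. It is not: the penalty comes from the definition of the outcome, and a follow-up-time offset does not remove it.

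Finally, only the abstinence outcomes are powered, and the count will be reported beside them. This limits the harm.

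**Conclusion.** The point holds as a limit on interpretation. A raw attempt count is fixed as a primary outcome, and it is not monotone in benefit. At the planned abstinence rates the ratio could be about 0.84 to 0.91 against PrOMOTE, provided that non-abstainers (version B), or the attempters among them (version A), average 2 to 3 attempts, abstainers make one, and attempting is equally common in both arms. None of these attempt rates is in the article. At an average of one the reversal is gone; below one (version B) the count favours PrOMOTE.

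The follow-up effect is separate and smaller: 1.06 to 1.08 at the assumed retention gap, in PrOMOTE's favour, and zero if retention is equal.

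A reader might go further and conclude that the trial will probably show PrOMOTE failing on this outcome, or that the analysis is invalid as written. The article supports neither. The direction depends on undocumented inputs, and the two powered outcomes are unaffected. The change is a worthwhile, cheap improvement and not a condition for the trial to be sound.

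**What to change.** 1. Report at least one 24-hour quit attempt by Week 12 (yes/no, all randomised, same logistic model as abstinence) beside the count, as the interpretable quit-attempt summary. State how a participant who leaves with no recorded attempt is classified, since this summary also depends on observed follow-up.
2. Fit the count model with log(weeks covered by completed calendars) as offset, and keep the planned switch to negative binomial. The offset deals with unequal follow-up only; it does not remove the penalty on sustained quitting.
3. State in advance that a lower count is not read as failure without the abstinence results.

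The data are already collected every two weeks, so the cost is wording and one more reported analysis. The yes/no summary discards some information, which is why the count stays. The registered outcome need not be replaced.

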Adverse events will be assessed every 2 weeks via REDCap, and participants will be asked to rate their self-reported physical health problems as “mild,” “moderate,” or “severe.” If participants endorse any of their symptoms as being “severe” in nature, and they also endorse using smoking cessation pharmacotherapy, REDCap will trigger a notification that is sent to the research staff and the clinical pharmacist who will review the report and assess whether follow-up with the participant is required. The alert can also be triggered if the individual requests a provider phone call to discuss mild to moderate symptoms that occur in conjunction with pharmacotherapy use.

Participants will be assessed for anxiety and depressive symptoms (Patient Health Questionnaire-4 [PHQ-4][54]), cognitive decline (BRFSS[43]), and quality of life (WHO Quality of Life-Brief Version [WHOQOL-BREF][55]) at baseline and 12-week and 24-week follow-up. Suicidal ideation that may arise due to changes in mood when quitting smoking will be monitored using a single item question: “In the past two weeks, have you been thinking about killing yourself?” If “yes,” REDCap will trigger a notification that is sent to a clinical psychologist on the Tobacco Treatment Program team.

A visual analog scale (VAS) will assess the proportion of ART doses taken in the past 30 days.[56] The instructions read: “Place a mark on the line below at the point showing your best guess about how much of your ART medication you have taken in the last month (e.g., 0% means you have taken no medication 50% means you have taken half your medication; 100% means you have taken every single dose of medication). The VAS will range from 0 to 100 in 10% intervals.

Biochemical verification of abstinence will be obtained at the Weeks 12 and 24 follow-up using breath carbon monoxide (CO) measurements.[57] A breath CO monitor will be mailed to the participants with instructions for use with a webcam if needed. At a prearranged time, participants will be sent a telehealth video link. Participants will virtually meet with research staff, and will complete the breath CO sample live so that it can be confirmed the participant provided the sample and reduce the chance of sample falsification. The CO device will also email a report of the CO test result to the research staff. If the participant does not have internet capabilities, and therefore cannot use these devices virtually, the breath CO sample will be collected in person.

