### Exploratory outcomes

Exploratory outcomes include 7-day PPA at study follow up (Week 24) as well as the effect of abstinence on CD4/CD8 cell counts and HIV-1 RNA viral load. Participants will be asked “Have you smoked a cigarette or used any type of combustible tobacco products in the past 7 days?” coupled with a breath CO ≤ 5 ppm to determine abstinence. CD4/CD8 cell counts and HIV-1 RNA viral load will be measured at study baseline and follow up.

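### The exploratory abstainer comparison on CD4/CD8 and viral load chooses its covariates by observed association with abstinence, which leaves a small, avoidable risk of residual confounding

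*Protocol article*

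**What the plan says.** Under Exploratory outcomes, the protocol article lists Week 24 abstinence "as well as the effect of abstinence on CD4/CD8 cell counts and HIV-1 RNA viral load". Under Planned analyses it says that "changes in CD4 and CD8 cell counts and the proportion of participants with detectable vs. undetectable HIV-1 RNA viral load will be examined" from baseline to Weeks 12 and 24, and that "participants who do and do not achieve abstinence will be compared at each timepoint". The models are generalized linear mixed models, and the covariate rule is "Model covariates will include baseline characteristics that were associated with follow-up abstinence".

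That sentence gives no threshold. The general rule at the start of the same section does refer to significance: "Characteristics found to be significantly associated with primary outcome measures will be included as covariates in the initial stages of adjusted model development".

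Several likely drivers of immune status are collected under Measures. "The Medication Adherence Questionnaire (MAQ) will be completed at baseline", and "Participants will also verify their list of current medications, including ART regimen". AUDIT-C and DAST-10 are baseline measures too. For ART specifically, "A visual analog scale (VAS) will assess the proportion of ART doses taken in the past 30 days"; the article does not say when. None of these is tied to the CD4/CD8 and viral load models.

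**The concern.** Randomisation does not balance quitters against continuing smokers. A participant who takes medication reliably, or drinks less, may be more likely both to quit and to have a suppressed viral load. To read the comparison as an effect of abstinence, such common causes must be in the model.

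A confounder is related to the exposure and to the outcome. The stated rule tests only the first relation, in the trial's own data, with few abstainers. Two things follow:

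- A confounder of modest strength is often missed by chance, and its bias stays in the estimate.
- A strong driver of CD4 or viral load that is unrelated to quitting is nearly always left out. This causes no bias, but it forgoes precision.

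At stake is the reading of one exploratory result. The primary and secondary comparisons do not depend on it.

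**Working it through.** **The plan's own figures.** The article gives no figure for this analysis. Its sample size for abstinence reproduces with unpooled variance, two-sided 5% and 80% power, where (1.96 + 0.8416)² = 7.849:

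- 15% vs 32%: (0.1275 + 0.2176) × 7.849 / 0.17² = 93.7, so 94 per arm (stated: 95).
- 10% vs 25%: (0.0900 + 0.1875) × 7.849 / 0.15² = 96.8, so 97 per arm (stated: 97).
- Attrition of 15%: 97 / 0.85 = 114.1, so 115 per arm (stated: 115).

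These figures only supply the expected number of abstainers.

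**Inputs from Power and sample size.** 115 per arm, with 7-day abstinence of 15% and 32%. Abstainers: 115 × 0.15 + 115 × 0.32 = 54.05, about 54. Others: 230 − 54 = 176.

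**Assumptions, not in the documents.** A two-sided 5% screen; a confounder whose true mean differs by d = 0.2 to 0.5 SD between the groups; a correlation of 0.4 with the outcome.

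**Step 1: chance that the screen misses the confounder.** SE of a standardised difference = √(1/54 + 1/176) = 0.156. The confounder is dropped when its observed difference is below 1.96 × 0.156 = 0.305 SD.

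**Step 2: imbalance left when it is dropped.** A dropped confounder has, by selection, a smaller than average observed difference. With β = (0.305 − d)/0.156, and the negligible lower tail ignored, the mean difference given omission is d − 0.156 × φ(β)/Φ(β). For d = 0.3: β = 0.03, φ = 0.399, Φ = 0.513, so 0.3 − 0.156 × 0.778 = 0.179 SD.

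**Step 3: bias.** Bias when dropped = 0.4 × that mean. Average bias = this × probability of omission (taking bias as zero when the confounder is included).

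| d (SD) | Dropped | Mean difference if dropped | Bias if dropped (SD) | Average bias (SD) |
|---|---|---|---|---|
| 0.2 | 75% | 0.13 | 0.05 | 0.04 |
| 0.3 | 51% | 0.18 | 0.07 | 0.04 |
| 0.4 | 27% | 0.21 | 0.08 | 0.02 |
| 0.5 | 10% | 0.23 | 0.09 | 0.01 |

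For d = 0.3 the average bias is 0.037/0.156 = 0.24 standard errors of the comparison, or 0.072/0.156 = 0.46 when the confounder is dropped.

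**Step 4: simulation for one confounder.** 4,000 trials of 230 per scenario, true effect zero, correlation 0.3 or 0.5. Under the screen, average bias was 0.03 to 0.05 SD at d = 0.2 to 0.3 and about 0.01 SD at d = 0.5. Type I error was 0.044 to 0.060. Always adjusting gave bias of at most 0.006 SD and type I error of 0.047 to 0.053. Never adjusting gave bias up to 0.25 SD and type I error up to 0.35.

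**Step 5: several confounders in one direction.** Four independent confounders, each 0.20 to 0.25 SD apart and correlated 0.3 with the outcome (illustrative values). The screen drops 64% to 75% of them, bias is about 0.12 SD, and type I error is about 0.12. Always adjusting gives bias near 0 and type I error of about 0.05.

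**Step 6: sensitivity.** At the continuous-abstinence rates, 115 × 0.10 + 115 × 0.25 = 40.25, about 40 abstainers. The SE is √(1/40 + 1/190) = 0.174, and the screen misses a 0.2 SD confounder in 79% of trials and a 0.3 SD confounder in 59%.

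**Step 7: precision.** A driver unrelated to abstinence is left out about 95% of the time. If it correlates 0.4 with the outcome, including it would cut the residual variance to 1 − 0.4² = 0.84 and the standard error to √0.84 = 0.92 of its value.

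**The case against.** The case for leaving the plan alone is fair in several respects.

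- **The rule screens on a relevant property.** A variable unrelated to abstinence cannot confound. If better ART adherers do quit more often, baseline adherence is what the rule looks for, and a 0.5 SD difference is caught about 89% of the time. This stands. A reader might infer that the rule gives no protection. It does: for one confounder it removes most of the bias that no adjustment would leave.
- **The bias is not the unadjusted one.** A reader might multiply 0.3 by 0.4 and expect 0.12 SD. That is the bias from never adjusting. The screen drops the confounder only when its observed difference is small.
- **The wording is not exclusive.** The sentence says what the covariates will include, not that nothing else may enter. The adherence questionnaire and the ART regimen are eligible. This stands, but eligibility does not secure a place.
- **Change scores help.** Analysing change in CD4 and CD8 removes stable differences between people. It does not remove confounding of the change itself, and viral load is analysed as detectable or not.
- **The visual analog scale cannot simply be forced in.** The article does not say when it is taken. Measured during or after the abstinence period, it may be affected by quitting. This stands and limits the fix.
- **A condensed article may leave the covariate list to an analysis plan.** That would excuse a missing list. Here the article states a rule, and the rule can be improved.

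**Conclusion.** The point holds as a minor one. The article fixes a data-driven rule, based on the exposure alone, for a non-randomised comparison that it words as an effect.

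With about 54 abstainers and an assumed 5% threshold, the rule misses a 0.2 to 0.3 SD confounder in about 75% to 51% of trials. With an assumed outcome correlation of 0.4, one such confounder leaves about 0.04 SD of bias on average, and 0.07 SD in trials where a 0.3 SD confounder is dropped. Type I error then stays near nominal. It rises to about 0.12 only in the illustrative case of four modest confounders in one direction. The differences and correlations are assumptions, since the documents give none.

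The documents do not support the stronger reading that the result will be seriously confounded or that ART adherence is shut out. Nor do they show that such confounders exist in this population. The outcome is exploratory, and no power calculation or primary conclusion rests on it.

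**What to change.** Replace the screen with a set of baseline covariates named in advance and chosen for their relation to the outcome: the baseline CD4/CD8 or viral load value, baseline medication adherence, ART regimen, AUDIT-C, DAST-10, age, sex and randomised arm. Arm belongs there because it changes quitting by design, and pharmacist contact might affect these outcomes by other routes; the plan should give that reason.

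Use the ART visual analog scale as a covariate only if it is measured before the abstinence period. Otherwise keep it for a sensitivity analysis.

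Report the randomised PrOMOTE vs TAU contrast for CD4/CD8 and viral load beside the abstainer comparison, and describe the latter as an association.

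The cost is a change of wording and a few more covariate degrees of freedom. The listed baseline variables are already collected. With about 54 abstainers the list should stay short, above all for the binary viral load outcome.
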